**Fig 3. Study Design and Procedure**

*The upper portion indicates the overall study design. The middle portion indicates the timeline for assessment of scales and EEG at baseline and post-intervention, also follow-up time-points. Brief mindfulness and relaxation training was administered to intervention group and control group after recruitment.Baseline assessment (-T2, -T1) was finished before intervention. Audio guidance was delivered for everyday's practice for BMT group. There is no other practice and intervention for control group after training. The lower portion indicates modules of psychological and behavioral assessments during the baseline and 5 follow-up sessions. Executive function measurement was implemented via EEG tasks including Stroop, More-odd Shifting, N-back. INT: intervention, INST:monthly intensive training (red triangle); rs-EEG: resting-state EEG; BMT: brief mindfulness training; VAS: Visual analogue scale; SMT: state-mindfulness.*

1. ***Sample size estimation. [List the four elements: δ(Δ) or π1, π2, α, β or Power, and provide the calculation formula]***

In this trial, Stroop reaction time related to executive function will be used as the primary indicator, and the sample size estimation will be conducted using the pwr package in R software. It is set that δ(Δ)tot = 125, corresponding to an expected reduction of 125ms in reaction time for the experimental group after the intervention. Additionally, α is defined as 0.05 and β as 0.80.

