The estimation of Cohen's d is required, with the formula Cohen's d = (δ(Δ) / SDestimate). Referencing studies in similar populations [<https://www.ncbi.nlm.nih.gov/pmc/articles/PMC8939409/>], SDestimate is taken as 250. Therefore, the relevant command is pwr.t.test (d = cohen_d, sig.level = 0.05, power = 0.80, type = "paired", alternative = "two.sided"), resulting in a sample size estimate of 34. Thus, the estimated sample size for the experimental group should be no less than 34 individuals; considering a natural dropout rate of 20%, the sample size for the experimental group should be at least 41 individuals. A ratio of 2:1 will be used to include 20 recreational gamers in the intervention group. A total of 61 participants are required for the intervention group. In order to maintain appropriate comparability, we will recruit an additional 61 participants with matching demographic profiles and equivalent levels of IGD (Internet Gaming Disorder) severity for the control group. Thus, the study demands a cumulative participation of 122 individuals in total.

1. ***Methods of randomization and concealed allocation. [Randomization is used to reduce the risk of selection bias. Methods for generating random number sequences include computer software, random number tables, semi-random or pseudo-random methods (such as using dates, birthdays, or even/odd numbers of hospital visits). Please describe the individuals involved in generating random number sequences and the methods they use. Concealed allocation is used in treatment studies to reduce the risk of selection bias. Key steps in concealed allocation include having a designated person determine the allocation sequence, ensuring that this person is not involved in enrolling participants, and securely storing the allocation table. Please provide detailed descriptions of these steps. Central randomization is a robust method of concealed allocation. Describe the individuals and methods involved in determining the allocation sequence]***

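### The 20% dropout allowance is too small: 41 enrolled less 20% leaves about 33, below the protocol's own minimum of 34

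*Protocol*

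**What the plan says.** In its sample size section the protocol plans on Stroop reaction time, with an effect of 125 ms, "corresponding to an expected reduction of 125ms in reaction time for the experimental group after the intervention", and a standard deviation given as "SDestimate is taken as 250". The R command specifies a paired, two-sided t-test at the 0.05 level with power 0.80. (The text just before it says "α is defined as 0.05 and β as 0.80"; the command shows that 0.80 is meant as power.)

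The result is 34, which the protocol treats as a floor: "Thus, the estimated sample size for the experimental group should be no less than 34 individuals". It continues: "considering a natural dropout rate of 20%, the sample size for the experimental group should be at least 41 individuals". No inflation formula is given.

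The remaining targets follow from 41. Twenty recreational gamers are added at 2:1, giving 61 in the intervention group. An equal control group brings the total to 122.

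**The concern.** A dropout allowance should leave the required number after the expected losses, so the required number is divided by the fraction retained. Here the protocol states the floor, the dropout rate and the enrolment figure together, and the enrolment figure does not return the floor at that rate. The stated 80% power is therefore not delivered under the protocol's own planning assumptions, even for the test it chose.

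Dropout does reduce the number analysed in this trial. The section on participant effectiveness leaves voluntary withdrawals out of the analysis, excludes the data of suspended participants from the final analysis, and provides for exclusion (or mixed-model adjustment) of those attending fewer than five sessions. The statistical methods section plans an intention-to-treat analysis as well. But a participant with no post-intervention Stroop measurement contributes no observed pre-post difference to the paired test on which the size is based.

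**Working it through.** **Inputs (all from the protocol's sample size section).** Difference 125 ms; SD 250; two-sided alpha 0.05; power 0.80; paired t-test; minimum 34; dropout 20%; enrolment 41.

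**Step 1: reproduce the base size.** d = 125/250 = 0.5. For a paired t-test, power is the probability that a noncentral t variable, with n − 1 degrees of freedom and noncentrality d√n, falls outside ± the 97.5% point of t with n − 1 degrees of freedom. Solving for 80% power gives n = 33.37, rounded up to 34. The protocol's figure reproduces.

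**Step 2: reproduce 41.**

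| Rule | From 34 | From unrounded 33.37 |
| --- | --- | --- |
| Multiply by 1.2 | 40.8, so 41 | 40.04, so 41 |
| Divide by 0.8 | 42.5, so 43 | 41.7, so 42 |

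Only multiplication by 1.2 gives 41. Since no formula is printed, this is an inference about how the figure arose. Step 3 does not depend on it.

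**Step 3: apply the stated dropout to the stated enrolment.**

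- 41 x 0.8 = 32.8 expected completers, about 33, against a floor of 34.
- Dropout that 41 can absorb: 41 − 34 = 7 losses, and 7/41 = 17.1%.
- Enrolment that meets the floor: 42 x 0.8 = 33.6 (short of 34); 43 x 0.8 = 34.4 (enough).

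**Step 4: power of the protocol's own test at d = 0.5.**

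| Completers | Power |
| --- | --- |
| 32 | 78.2% |
| 33 | 79.5% |
| 34 | 80.8% |

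So 34 is the smallest whole number that reaches 80%, and 33 just misses.

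**Step 5: chance of reaching the floor.** If each participant drops out independently with probability 0.20 (an assumption made here, not in the protocol), the number retained is binomial. The probability of keeping at least 34 is 40.7% from 41 enrolled and 64.7% from 43.

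**Step 6: what depends on 41.** 41 + 20 = 61 per group, and 61 x 2 = 122 in total.

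**The case against.** The strongest objection is one of scale. Expected completers fall short by 1.2 against 34, or by about 0.6 against the unrounded 33.37, and power at 33 is half a point under target. The SD of 250 is a single value taken from an outside study, and no source is given for the 20%; uncertainty in either could easily exceed the discrepancy. That stands, and it limits the weight of the point. It does not make the figures consistent.

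The 1.2 multiplication is inferred. That is also correct, but the contradiction is there however 41 was reached.

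The protocol sets 41 as a minimum, which would permit 43. This helps little, because the totals of 61 and 122 are then fixed from 41 exactly.

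Finally, 34 comes from a within-group paired test, although the study design section aims at superiority over the control group. If the size is recalculated for a between-group comparison, both 34 and 41 will be replaced. That is a fair reason to make both corrections together. The dropout step would still have to be done by division, and any between-group power restated for the present enrolment should start from about 33 completers, not 34.

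**Conclusion.** The statement is wrong as written. At the protocol's own 20% dropout, 41 enrolled leaves about 33, below its own minimum of 34, and expected power for its own paired test is 79.5% instead of at least 80%. The gap is two enrolled participants (43 against 41), or about 1.3 percentage points of power between 34 and 33 completers.

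This takes d = 0.5, the 20% rate and the paired test as the protocol gives them, and it treats dropouts as contributing no pre-post difference. It does not endorse 34 as the right base size. The mismatch between the paired test and the between-group aim is a separate and larger matter. The error is minor but should be corrected, because every recruitment target in the section rests on 41 and the protocol says the trial has not yet begun.

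**What to change.** Keep 41 and correct the statement, for example:

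> Enrolling 41 allows for 17% dropout. At 20% dropout about 33 participants remain, and power is just under 80% for the paired test.

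This costs one sentence and a slightly less favourable stated figure, and needs no extra participants. Use 33 completers when between-group power is restated.

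If the sponsor prefers to hold the floor of 34 at 20% dropout, the enrolment figure is 34/0.8 = 42.5, so 43, and the dependent figures change. At 2:1, 43/2 = 21.5 recreational gamers. Rounding down, as the protocol did with 41/2 = 20.5, gives 21, hence 43 + 21 = 64 per group and 128 in total, six more than planned. Rounding up gives 22, 65 and 130, eight more than planned.

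Whichever is chosen, state the inflation formula, n/(1 − dropout), in the protocol.

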1. ***Study design, design pattern diagram, with SPIRIT template attached. [Clearly state the design scheme used in this study, such as: consecutive case or single-arm design, cross-sectional study, case-control study, cohort study, including historical cohort study or prospective cohort study, nested case-control study, randomized controlled trial, clearly specify the type, such as parallel design, crossover design, factorial design, single-group design; for treatment studies, specify the type of research objective framework, such as superiority, equivalence, non-inferiority, exploratory]***

The current trial adopts a randomized controlled parallel design, with substantial literature supporting the moderate effect of brief mindfulness interventions on executive function [[5](#_ENREF_5" \o "Zhou, 2020 #694)]. Therefore, for the IGD population, this trial aims to demonstrate superiority under the condition of a brief mindfulness intervention compared to the control group. The trial comprises four stages: participant recruitment, baseline assessment, post-intervention measurement, and follow-up assessment, with corresponding evaluations conducted at the conclusion of each phase. A schematic diagram of the design is depicted in **Fig 3.** The trial has not yet commenced, and it is estimated that the entire process from initiating participant recruitment to completing data analysis and manuscript writing will take approximately one year.

**
[figure not shown]
**

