(1) In this study, the intervention period focused on breath meditation lasts for one week and serves as a concise mindfulness behavior training. The study will involve a baseline collection of EEG and other relevant data for all participants, a one-week training on the intervention content, collection of post-intervention EEG and other relevant data, and follow-ups (one week, one month, four months, six months, and one year after data collection post-intervention). During the follow-up phase, participants will undergo multiple mindfulness training sessions. Grouping will occur after the baseline data collection for participants is completed.

(2) The breath meditation training is the primary intervention method employed in this study. The design includes grouping into an experimental group and a control group: the experimental group (breath meditation training) and the control group (relaxation training). The recruited participants are from the same school, and their connections make it challenging to implement the criteria for double-blind randomization.

(3) The randomization process for this trial will utilize the random sequence generator available at random.org.

1. ***Blinding. [Blinding is used in treatment studies and diagnostic trials to reduce the risk of implementation bias and measurement bias. Implementing strict confidentiality measures, such as using placebos or simulating procedures, is an effective blinding method. If blinding is necessary and feasible for your study, describe the methods and procedures for implementing blinding]***

This trial involves group therapy, with participants being students from the same school. Therefore, it is possible that among participants who may know each other or even among those who do not, conversations related to the experimental training they are undergoing may arise. Additionally, maintaining blinding for the researchers is quite challenging, as they can easily be influenced by information related to the experiment during the process. As a result, it is not feasible to meet the double-blind requirements of clinical trials.

1. ***Outcome Measures. [Outcome measures are used to evaluate the results of a study and can include primary, secondary, and safety measures, including adverse events and reactions. Please describe the names of the measures, the methods of measurement, and the time points at which they are assessed]***

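### The sample size section recruits a matched control group, which contradicts randomisation after baseline, and no stratification by IGD status is described to secure the planned 41/20 split per arm

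*Protocol*

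**What the plan says.** Three parts of the protocol describe how the arms come about.

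- **Study design:** "The current trial adopts a randomized controlled parallel design". The aim is placed in one subgroup: "for the IGD population, this trial aims to demonstrate superiority under the condition of a brief mindfulness intervention compared to the control group".
- **Sample size estimation:** the intervention group needs 41 IGD participants and, at 2:1, 20 recreational gamers, 61 in all. For the other arm, "we will recruit an additional 61 participants with matching demographic profiles and equivalent levels of IGD (Internet Gaming Disorder) severity for the control group". The total is 122.
- **Methods of randomization and concealed allocation:** "Grouping will occur after the baseline data collection for participants is completed", and "The randomization process for this trial will utilize the random sequence generator available at random.org".

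The SPIRIT flowchart places allocation at the second baseline timepoint, after screening and consent. The participant recruitment section takes eligible people in the order they come forward and mentions no matching step. No section mentions strata, blocks, an allocation ratio or who holds the list.

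**The concern.** The sample size sentence assigns people to a named arm at recruitment and gives matching as the means of making the arms comparable. In a randomised trial, chance does that work, after enrolment. Staff who followed the sentence literally would be running a matched, non-randomised comparison. Matching on demographics and IGD severity leaves open everything not matched on, such as when and through whom a student was recruited, or motivation to take up mindfulness training. All participants come from one school, and the protocol concedes that they may know each other and that researchers are hard to blind. A superiority claim would then rest on the absence of unmeasured confounding.

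The second matter is smaller. The plan fixes the IGD/recreational mix of the intervention arm, implies the same mix for the control arm, and aims its superiority claim at IGD participants. Yet no described allocation step secures that mix.

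**Working it through.** **1. The plan's own figures.** Inputs from the sample size section: "corresponding to an expected reduction of 125ms in reaction time for the experimental group after the intervention"; "SDestimate is taken as 250"; "α is defined as 0.05 and β as 0.80" (the 0.80 is entered as power in the stated command); paired two-sided t-test; 20% dropout.

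- d = 125/250 = 0.5. The paired t-test gives n = 33.37, so 34, as stated.
- 34 × 1.2 = 40.8, so 41, as stated.
- Recreational gamers at 2:1: 41/2 = 20.5, taken as 20. Then 41 + 20 = 61 and 2 × 61 = 122, as stated.

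The arm sizes reproduce. The conflict lies in how the second 61 is obtained.

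**2. The two rules side by side.**

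| | Sample size section | Study design and randomisation sections |
|---|---|---|
| When the arm is fixed | At recruitment | After baseline measurement |
| What decides the arm | Being recruited as a match | A random sequence |
| What makes arms comparable | Matching | Chance |

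No order of steps satisfies both columns.

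**3. IGD split if allocation is random but unstratified.** Assume enrolment of 2 × 41 = 82 IGD and 2 × 20 = 40 recreational gamers, with arms fixed at 61/61. The protocol gives no enrolment quota by IGD status, so this is an assumption. The number of IGD participants in one arm, X, is hypergeometric (122 in total, 82 IGD, 61 drawn).

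- Mean = 61 × 82/122 = 41.
- SD = √[61 × (82/122) × (40/122) × (61/121)] = 2.60.
- P(X = 41) = 15.3%.
- P(X within 3 of 41) = 82.3%; within 5 = 96.7%.
- 95% range: 36 to 46. At the edge, the arms hold 36 IGD + 25 recreational and 46 IGD + 15 recreational.
- P(either arm has fewer than 34 IGD at allocation) = 0.4%.

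**4. Effect on power.** For illustration only, take d = 0.5 as a between-arm effect in a two-sided two-sample t-test at 0.05 among 82 IGD participants. Power is 60.9% at 41/41 and 60.3% at 36/46, a loss of 0.6 percentage points. The level of about 61% reflects sizing a between-arm aim with a within-arm test, which is a separate matter; only the difference is relevant here.

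**5. With stratification.** Separate lists, each balanced to its total, give 82/2 = 41 IGD and 40/2 = 20 recreational gamers per arm by construction.

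**The case against.** The strongest reply is that the matching sentence is loose drafting. It sits in a sample size section, takes the count from 61 to 122, and may mean only that the control arm should have the same composition. It describes no matching procedure and does not say that the intervention arm is filled first. The study design section, the randomisation section, the flowchart and the recruitment section all point towards one pool allocated after baseline. This is a plausible account of the intent. It does not remove the conflict, because the sentence still speaks of recruiting people for the control group and offers matching as the route to comparability.

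The reply succeeds against several stronger readings that a reader might infer:

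- *That the trial is non-randomised.* This follows only if one sentence overrides the other sections. The text is contradictory, not settled that way.
- *That the sequence is unstratified.* The protocol names a generator and is otherwise silent; random.org can be run once per stratum.
- *That the 41/20 split will not occur.* It is the expected split, and with 61/61 arms the count is within 5 of 41 in about 97% of allocations.
- *That imbalance could be as wide as under coin-toss allocation* (95% range 32 to 50 IGD per arm). That scheme does not fit a plan with 61 per arm.
- *That the staff who enrol also control the list.* The research team section puts recruitment, data collection and analysis on one role line, but nobody is named as generating or holding the sequence. The section's own template asks for this and it goes unanswered. That is missing detail, not a shown error.

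It is also fair that unstratified randomisation is valid, and that a comparison within IGD participants stays unbiased whatever the recreational split.

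**Conclusion.** The contradiction is real and needs correcting before recruitment: the control group cannot be both recruited by matching and formed by random allocation after baseline. The bias under a literal reading of the sample size section cannot be bounded from the document. Whether it would arise depends on which section staff follow, and the protocol leaves that open.

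The missing stratification is secondary. Assuming 82 IGD and 40 recreational gamers and arms fixed at 61/61, 41 IGD per arm is expected with SD 2.6 and a 95% range of about 36 to 46, and the power cost is under one percentage point in the illustration. If enrolment departs from 82/40, the mix per arm could differ further. Stratifying is worthwhile because it is cheap and the plan itself relies on the mix, not because its absence would invalidate the trial.

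**What to change.** Replace the matched-recruitment sentence in the sample size section with a statement that one pool of 122 (82 IGD, 40 recreational gamers) is recruited, measured at baseline and then randomised 1:1. In the randomisation section, specify separate random.org lists for the IGD and recreational strata, each balanced to its planned total (41/41 and 20/20). Include the stratum as a term in any analysis that pools the two. In the same edit, state who generates and holds the lists, since the section's template asks for it.

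The cost is protocol wording and two lists instead of one, with no additional participants. The study design section says the trial has not begun, so the change can be made before anyone is enrolled.

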(1) Primary indicators: average daily gaming time (self-reported by participants), Five Facet Mindfulness Questionnaire (FFMQ), Internet Addiction Test (IAT), Game Craving Scale (adapted from QSU-Brief), Adolescent Executive Functioning Scale (EFS-A), Barratt Impulsiveness Scale, State Mindfulness Scale, Game Craving Visual Analogue Scale, behavioral data, and EEG data (from EEG equipment).

(2) Secondary indicators: Self-Rated Sleep Status Scale, Depression-Anxiety-Stress Scale (DASS-21), Positive and Negative Affect Schedule (PANAS).

(3) Safety indicators: Researchers will inquire daily during the intervention period whether participants experience any adverse reactions. If there are any adverse reactions, they will communicate in person or by phone with the research staff.

Measurement time points are detailed in item 5.

1. ***Definition of Participant Effectiveness Determination. [This includes definitions for participant withdrawal, exclusion, loss to follow-up, confounding factors, study discontinuation, and study suspension]***

(1) Participant Withdrawal: Each participant can withdraw from the study at any time during the experiment without providing any reason. Participants who withdraw voluntarily will not be included in the analysis. Under the conditions of a mixed study, we have a complete access procedure for withdrawn participants. If participants are willing to provide a reason for their withdrawal, it will be recorded by the researchers.

(2) Participant Exclusion: If participants cannot consistently participate in the group interventions during the training process—where the focused breathing meditation training lasts one week—those who attend fewer than 5 sessions will be considered not fully intervened and should theoretically be excluded or adjusted using a mixed-effects model.

(3) Participant Loss to Follow-up: If any participant cannot be contacted for two consecutive attempts after the intervention is completed, they will be classified as lost to follow-up.

(4) Participant Contamination: After the intervention is completed, we will conduct a census of participants. If any participant in the control group attempts to learn about the training methods of the intervention group (or vice versa) and tries to train, they will be classified as contaminated participants.

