(5) Participant Termination: To ensure the health of the participants, any adverse events will constitute a termination condition. Researchers will discuss such situations with the affected participants to consider premature termination of their intervention. Appropriate clinical interventions will be provided to them with their consent.

(6) Participant Suspension: In this trial, we will allow participants to request suspension of their involvement in the intervention. If any requests for suspension are made, participants will be moved to a future intervention group after the trial team assesses that no adverse events or reactions have occurred. Data collected from these participants during the current trial will not be included in the final data analysis.

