8. Insert Active Electrodes: Correspondingly insert the labeled active electrodes into the designated electrode names marked on the EEG cap (make sure to carefully match the electrodes’ labels with the EEG cap). Wrap the CMS and DRL active electrode wires around the other electrodes' cables (3-5 wraps), and plug their connectors into the corresponding matching ports on the amplifier.
9. Confirm Connections and Start Data Collection: After confirming that the EEG software and hardware are properly connected, run the software to collect EEG data. Follow the software usage instructions and ensure the quality of the EEG data meets the required standards before starting the data collection. Save the EEG data to the computer or hard drive according to your naming format.
10. Intervention Content Training Process:

The researchers of this study will collaborate with professional psychological teachers to conduct a week-long intervention content training and multiple training sessions during the follow-up phase.Before each practice session begins, participants will be reminded of the time and location of the practice, and the researchers will conduct on-site check-ins. Training for the intervention content will be provided for one week by the teachers from the Student Mental Health Education and Counseling Center, along with multiple training sessions during the follow-up phase. Professional psychological teachers will guide the training, and the content practiced each day will be sent to the participants' group after each session for continued practice.

1. ***Statistical analysis methods. [Select appropriate statistical analysis methods based on the data type of each measurement variable. Include any additional methods for subgroup analysis or auxiliary analysis. If there are personnel reductions during the trial, indicate whether an intention-to-treat (ITT) analysis was used and compare it with per-protocol (PP) analysis]***

The primary and secondary indicators of this study's scales will be presented to participants in the form of paper questionnaires, while behavioral data and EEG data will be collected from participants using electroencephalography devices.

Demographic data and scale data analysis will use SPSS software, employing t-tests, covariance analysis, etc.; EEG data analysis will utilize Matlab_2013b software, EEGLab software, and scripts.

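### Training is delivered in groups, but the tests named for the scale outcomes and the sample size treat participants as independent; any within-group correlation would make standard errors too small

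*Protocol*

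**What the plan says.** **Delivery.** The Blinding section says: "This trial involves group therapy, with participants being students from the same school". It adds that participants may talk to each other about their training. The section on participant effectiveness determination, item 2, opens: "If participants cannot consistently participate in the group interventions during the training process". The standard operating procedures describe on-site check-ins and state: "Professional psychological teachers will guide the training". Each day's content is then sent to the participants' group for further practice.

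**Allocation.** "The randomization process for this trial will utilize the random sequence generator available at random.org". Grouping follows baseline data collection. Allocation appears to be by individual; no cluster randomization is described.

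**Analysis.** The statistical analysis section says: "Demographic data and scale data analysis will use SPSS software, employing t-tests, covariance analysis, etc". The Outcome Measures section lists several scales as primary, among them the mindfulness, internet addiction, craving, executive function and impulsiveness scales. The only mixed model in the protocol concerns people attending fewer than five sessions, who "should theoretically be excluded or adjusted using a mixed-effects model". It has no connection with training groups.

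**Sample size.** A two-sided paired t-test on Stroop reaction time (125 ms change, SD 250 ms, 80% power) gives 34. This becomes 41 with dropout, 61 per arm with 20 recreational gamers, and 122 in total.

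**Not stated.** The number and size of training groups, the number of teachers per arm and any intraclass correlation are not given. Training group and teacher are not among the listed data items.

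**The concern.** People trained together share a teacher, the same sessions and one another's influence. These act after allocation, so randomizing individuals does not remove the correlation they can create. A t-test or analysis of covariance that ignores it computes the standard error as if every participant contributed separate information. If the correlation is positive, the interval is too narrow and the test rejects too often. The sample size has the matching weakness: its power is that of independent participants.

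The Study design section claims superiority over control in the IGD population. A falsely precise between-arm comparison on the primary scales would bear directly on that claim.

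**Working it through.** **Step 1: reproduce the plan's figure.** Standardized effect d = 125 / 250 = 0.5. A paired t-test at two-sided 0.05 and power 0.80 needs n = 33.37, rounded up to 34, as stated. Then 34 × 1.2 = 40.8, rounded up to 41; 41 + 20 = 61; 2 × 61 = 122. No factor for clustering enters at any step.

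**Step 2: inputs for the check.** From the protocol: two-sided alpha 0.05 and 61 per arm. Assumed, because the protocol gives neither: training-group size m of 10 to 20 and intraclass correlation (ICC) of 0.01 to 0.05, equal in both arms.

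**Step 3: formulas.**
- Design effect: DE = 1 + (m − 1) × ICC.
- Standard error understated by a factor √DE.
- Actual two-sided error of a nominal 5% test: 2 × [1 − Φ(1.96 / √DE)].

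| m | ICC | DE | √DE | Actual error | 33.37 × DE, rounded up |
|---|---|---|---|---|---|
| any | 0 | 1.00 | 1.00 | 5.0% | 34 |
| 10 | 0.01 | 1.09 | 1.04 | 6.0% | 37 |
| 10 | 0.05 | 1.45 | 1.20 | 10.4% | 49 |
| 20 | 0.01 | 1.19 | 1.09 | 7.2% | 40 |
| 20 | 0.05 | 1.95 | 1.40 | 16.0% | 66 |

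The last column applies the design effect to the plan's own calculation, before dropout. There the ICC is that of the change in reaction time.

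**Step 4: check by simulation.** An ordinary two-sample t-test with 61 per arm (20,000 replicates per cell) gave 5.0% and 5.1% at ICC 0. With 7 groups per arm it gave 5.6% and 9.4% at ICC 0.01 and 0.05. With 4 groups per arm it gave 6.7% and 13.5%. These are slightly below the table because 61 / 7 = 8.7 and 61 / 4 = 15.3, so the simulated groups were smaller than 10 and 20.

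**Step 5: only one arm clustered.** Averaging the two arms' variances, the factor is (1 + DE) / 2.
- DE = 1.09: factor 1.045, error 2 × [1 − Φ(1.96 / 1.022)] = 5.5%.
- DE = 1.95: factor 1.475, error 2 × [1 − Φ(1.96 / 1.214)] = 10.7%.

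**Step 6: the information left.** For 61 per arm, 61 / 1.09 = 56.0 and 61 / 1.95 = 31.3. The superiority claim concerns the IGD participants, planned at 41 in the experimental arm: 41 / 1.09 = 37.6 and 41 / 1.95 = 21.0. This takes m as the number of IGD participants per group; in mixed groups that number, and so the loss, would be smaller.

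**The case against.** The strongest reply is that the size of the problem comes from two numbers the protocol does not give. That stands. At ICC 0 the error is exactly 5%, and with groups of 5 and ICC 0.01 it is 5.5%. A reader might infer that the stated tests certainly exceed 5%; the protocol supports this only if outcomes correlate within groups.

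The named tests cover demographic and scale data, and the list ends openly. No inferential test is named for Stroop reaction time, so one cannot say that a stated Stroop superiority test is invalid. This also stands. It leaves the primary scales and the sample size.

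A separate analysis plan could add a term for training group. That is fair for the model's details. It does not cover the sample size, which is fixed here without any allowance, or a grouping variable that is not among the data to be collected.

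Equal clustering in both arms is inferred. The Blinding section speaks of the whole trial, but the attendance rule is tied to the breathing training, and the Fig 3 note gives daily audio guidance to the mindfulness arm and no further practice to controls. Step 5 shows the smaller inflation if only one arm is clustered.

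A reader might also suppose that each arm is trained as one group. With 61 per group and ICC 0.05, DE = 1 + 60 × 0.05 = 4.0 and the error is about 33%. The protocol does not say this. The suspension rule, under which "participants will be moved to a future intervention group", hints at more than one group, though ambiguously.

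**Conclusion.** The point holds in conditional form. Training is group-based, the tests named for the scale outcomes assume independence, and the sample size includes no design effect. If outcomes correlate within training groups, standard errors are understated by a factor of about 1.04 to 1.40. The actual error is then about 6% to 16% at a nominal 5%, for assumed groups of 10 to 20 and ICC of 0.01 to 0.05 in both arms. If only one arm is clustered, the range is about 5.5% to 11%. For Stroop reaction time the finding is limited to the sample size: the 80% power is that of independent participants.

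The protocol does not establish that inflation will occur or that either arm is a single group. It also gives no basis for requiring several parallel groups per arm as a cheap correction: that is a change in delivery and may need extra teacher sessions.

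**What to change.** 1. Record each participant's training group and teacher, and state the number and size of groups per arm.
2. In the statistical analysis section, replace t-tests and covariance analysis for between-arm comparisons with a baseline-adjusted mixed model. Give it a random intercept for training group within arm and small-sample degrees of freedom (Satterthwaite or Kenward-Roger). If only one arm is trained in groups, apply the random term to that arm alone.
3. In the sample size section, state that the 80% power assumes independent participants, before any design effect.
4. If an arm is trained as a single group, state that arm and group effects cannot be separated by any model, and limit the conclusion accordingly.

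**Cost:** two recorded variables and revised wording, with no extra participants. Intervals will be wider and the stated power less favourable. With few groups the degrees of freedom are few: with k groups per arm, the between-group comparison has roughly 2 × (k − 1), so 12 with 7 groups per arm and 6 with 4.
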